### Data management

All data will be collected and recorded in case report forms (CRFs) by an investigator before transfer to the data management center. To ensure accurate data collection, after each patient has been visited, the CRF will be completed by an investigator who did not evaluate the patient. All demographic and baseline clinical data, as well as primary and secondary outcome measures, will be recorded in the CRF. All data will be checked, and any missing data will be obtained from the trial database or from participants. To ensure patient confidentiality, the CRF for each patient will be given an anonymous allocation number. We will obtain permission to continue follow-up and data collection in the event of withdrawal from the study. The responsible investigator must review and sign all completed CRFs. Afterwards, data will be statistically analyzed by a statistician who is unaware of the allocated treatment.

### Statistical methods

#### Sample size

The null hypothesis is that Pfannenstiel incision is not superior to periumbilical incision in terms of the average number of days it takes the donor to return to normal physical activity in the 4 weeks after surgery. We chose 10 days difference in return to normal physical activity as the minimal clinically important difference, because a difference of less than 10 days is not valuable enough to decide the standard surgical method. Therefore, we used a difference of 10 days for sample size calculation. The standard deviation is expected to be 13 days, according to the results of El-Galley et al. [15], who compared days to return to work between periumbilical and Pfannenstiel incision groups. However, we chose “days to return to normal physical activity” as the primary endpoint rather than “days to return to work” because the nature of patients’ work and their capabilities are different, and some of our living donors may be unemployed or housekeepers. A one-sided significance level of α = 0.05, a power of 80%, and a sample size of 44 patients (22 per group) are required to apply a two-sample *t* test (calculations performed with AddPlan 6.0). To account for a 15% drop-out rate, 26 patients will be enrolled in each study arm (52 patients in total).

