#### Primary endpoint

Patients will complete the Katz Basic Activities of Daily Living (ADL) self-maintenance questionnaire each day during the first four POWs until all normal activities are recovered. This questionnaire indicates their ability to perform daily living activities [19]. The Katz ADL evaluates the patient’s independent performance in six functions: bathing, dressing, using the toilet, transferring, continence, and feeding. These functions are evaluated with yes/no questions. A score of 6 indicates independence in all six functions, demonstrating normal physical activity. Since all donors are able to perform these basic activities before the operation, the Katz ADL questionnaires are not administered prior to surgery. The questionnaires will be gathered at each follow-up visit, and the number of days it takes to return to normal physical activity will be determined based on the answers. The primary endpoint has been defined as the number of days from surgery until return to normal physical activity.

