## Discussion

LDKT is one of the best solutions for organ shortage. Since living kidney donors give others a second chance to live, it is very important that they undergo the safest possible surgical procedure with the lowest risk and complication rate. Although both HALDN procedures (periumbilical and Pfannenstiel) are accepted surgical approaches [22–25], these two different incision methods have not been compared in an RCT. This RCT was initiated to compare the outcome of periumbilical and Pfannenstiel incisions.

Only one RCT has compared HALDN using a periumbilical incision with pure laparoscopic donor nephrectomy using a Pfannenstiel incision for graft extraction [26]. The authors compared operation time, warm ischemia time, complications, and quality of life between the two groups, but they did not report the time it took for the donor to return to work/normal physical activity or wound appearance. This RCT also compared two different methods (pure laparoscopy versus HALDN) as well as two types of incision. There are also some published non-randomized or retrospective studies that compare periumbilical and Pfannenstiel incisions for hand assistance and/or kidney removal in HALDN or laparoscopic donor nephrectomy [15–18]. However, although El-Galley et al. [15] reported the time to return to normal activity and work, none of these studies evaluated the donor’s comfort and satisfaction; they mainly compared the occurrence of complications and length of hospital stay after the two procedures.

The HAPERPACT trial will be the first RCT to evaluate the impact of periumbilical and Pfannenstiel incisions on donor recovery. We will compare the time it takes for the donor to return to normal physical activity after the two different procedures. This will indicate patient satisfaction and comfort, as well as the influence on economy and burden of disease.

The secondary findings of this RCT will compare the intraoperative and postoperative results in living kidney donors. The HAPERPACT trial is novel in that it investigates all factors associated with donor satisfaction after nephrectomy, including postoperative pain, rescue analgesics, PEFR, physical activity (using IPAQ), length of hospital stay, time to return to work, patient satisfaction, and cosmetic score. To ensure that our findings are more encyclopedic, the quality of the transplanted graft and graft function in recipients will also be monitored in this trial.

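### The planning SD of 13 days is borrowed from return to work and cannot, or can barely, occur with a 10-day difference on a 28-day Katz scale, so the stated 80% power does not describe the primary endpoint

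*Protocol article*

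**What the plan says.** Under Sample size, the protocol article sets the target effect itself: "We chose 10 days difference in return to normal physical activity as the minimal clinically important difference". It adds that a smaller difference would not justify choosing one incision as the standard. For the variability it says "The standard deviation is expected to be 13 days" and cites an earlier study "who compared days to return to work between periumbilical and Pfannenstiel incision groups". The next sentence explains why return to work was not made the primary endpoint: donors' jobs and capacities differ, and some have no paid work. The result is given as "A one-sided significance level of α = 0.05, a power of 80%, and a sample size of 44 patients (22 per group" for a two-sample t test, raised to 26 per arm (52 in total) for 15% dropout.

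Under Primary endpoint, the outcome is the number of days to full independence on six basic functions: "A score of 6 indicates independence in all six functions, demonstrating normal physical activity". Donors complete the questionnaire "each day during the first four POWs until all normal activities are recovered". The Abstract and the null hypothesis under Sample size give the same four-week window.

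The Discussion says that the study supplying the SD also "reported the time to return to normal activity and work".

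**The concern.** The SD belongs to an outcome that the protocol rejects one sentence later, and it is not re-derived for the outcome that replaced it. The two differ in kind. Return to work is not confined to the four-week questionnaire window, whereas the Katz time is observed only inside it, and a bounded variable has a ceiling on its SD. If 13 days lies at or above that ceiling once the arms differ by 10 days, the planning inputs cannot both describe the primary endpoint.

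At stake is the only operating characteristic the protocol states. Readers will use 80% power for 10 days to judge what a significant or a null result means. If the real SD is well below 13, the trial reacts to differences much smaller than 10 days, which the protocol itself regards as too small to settle the choice of technique.

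**Working it through.** **Inputs from the protocol article.** Difference 10 days, SD 13 days, one-sided α 0.05, power 80%, two-sample t test, 1:1 allocation, 15% dropout (Sample size); recording window of four weeks, i.e. up to day 28 (Abstract, Primary endpoint, Sample size).

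**1. Reproducing the stated figure.** With n per arm, the noncentrality is 10 / (13 × √(2/n)) on 2n − 2 degrees of freedom. The noncentral t gives power 0.790 at n = 21 and 0.806 at n = 22, so 22 per arm is right. Dropout: 22 / 0.85 = 25.9, rounded up to 26.

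**2. Ceiling on the SD.** A variable confined to [a, b] with mean m has variance at most (m − a)(b − m). For two arms 10 days apart, the average of the two variances is largest when the means lie 5 days either side of the midpoint.

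- Days 1–28 (midpoint 14.5, means 9.5 and 19.5): √(8.5 × 18.5) = √157.25 = 12.54. SD 13 is impossible. Conversely, SD 13 in both arms allows a difference of at most 2 × √(13.5² − 13²) = 2 × √13.25 = 7.28 days.
- Days 0–28 (midpoint 14, means 9 and 19): √(9 × 19) = √171 = 13.08. SD 13 (variance 169) is just reachable. The slack is 171 − 169 = 2. A donor scored in whole days strictly between 0 and 28 uses up at least 1 × 27 = 27 units of it, so at most 2/27 = 7% of donors could have any value other than day 0 or day 28.

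For comparison, donors spread evenly over days 1 to 28 have an SD of √((28² − 1)/12) = 8.1.

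**3. What the design gives at feasible SDs.** The documents give no SD for the Katz time, so the SDs below are assumptions, apart from the two ceilings. By the noncentral t, the 80%-detectable difference is 0.762 × SD at 22 per arm and 0.699 × SD at 26 per arm. The smallest observed difference that reaches one-sided 5% at 22 per arm is 1.682 × √(2/22) × SD = 0.507 × SD.

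| SD (days) | Power for 10 days, 22/arm | 80%-detectable, 22/arm | 80%-detectable, 26/arm | Observed difference reaching significance, 22/arm |
|---|---|---|---|---|
| 13.08 (ceiling, days 0–28) | 0.80 | 10.0 | 9.1 | 6.6 |
| 12.54 (ceiling, days 1–28) | 0.83 | 9.6 | 8.8 | 6.4 |
| 10 | 0.95 | 7.6 | 7.0 | 5.1 |
| 8 | 0.99 | 6.1 | 5.6 | 4.1 |
| 4 | >0.99 | 3.0 | 2.8 | 2.0 |

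**The case against.** Four points can be made for the protocol.

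- **The calculation is right, and an SD that is too large is cautious.** This stands. On the recorded scale, power for a 10-day difference is at least 0.80 at either ceiling and rises as the SD falls. A reader might infer that the trial is underpowered; the documents do not support that. Low power appears only if the true difference is assumed to be a few days, or if the 10 days is taken to refer to uncapped recovery times that the window then shortens. In simulations of the latter (latent SD 13, assumed control means 15 to 45 days, values limited to days 1–28), power at 22 per arm ran from 0.48 to 0.77 for normal times and from 0.68 to 0.96 for gamma times. The protocol fixes none of these assumptions.
- **The 10 days is not borrowed.** This stands. A reader might infer that effect and SD both come from return to work. Only the SD does; the protocol declares 10 days as its own minimal important difference for normal physical activity.
- **Impossibility depends on the day count.** This stands in part. The article does not say whether day 0 can be scored, and with day 0 allowed the pair is possible. It then requires at least 93% of donors to sit at one of the two end points, which is no reasonable planning assumption. Both limits also assume that no donor is given a value above 28.
- **A significant result below 10 days can arise in any test of zero difference.** This stands in part. Even at SD 13, an observed 6.6 days would suffice. A smaller SD widens the gap between significance and the declared threshold.

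The Discussion's remark that the earlier study reported time to normal activity shows that a closer outcome was known. It does not show that a usable SD was available or that the measure resembled Katz ADL.

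**Conclusion.** The point holds as a fault in the inputs. SD 13 comes from a different outcome and, combined with a 10-day difference, exceeds the ceiling on days 1–28 (12.54) or all but touches it on days 0–28 (13.08). The stated 80% power is therefore not a description of the Katz endpoint. The sample size sum, the dropout inflation and the 10-day target are not in error.

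The consequence is one of interpretation. If the SD is clearly below the ceiling, power for 10 days exceeds 80%, and the trial can declare superiority on a difference that the protocol considers too small to decide the standard method. How far below 10 days depends on an SD that the documents do not give, so the figures at SD 4, 8 and 10 are illustrations. The bounds rest only on the 28-day window and on recorded times staying within it.

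**What to change.** Keep 52 donors. In the analysis plan, which the protocol says will be written by the end of recruitment, and in the final report:

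- State that SD 13 was a return-to-work proxy that does not fit the 28-day Katz scale. Keep it and the 10 days on record as the basis for the sample size, with that caveat. Dropping them would hide how the number was reached.
- Replace the single 80% figure with power and detectable difference at 22 to 26 per arm over a range of SDs feasible on this scale, as in the table above.
- If wished, inform the range with an SD pooled without arm labels. Note that it includes any difference between arms: a within-arm SD of 4 with a 10-day gap would appear as √(4² + 5²) = 6.4.
- Keep 10 days as the pre-declared minimal important difference rather than resetting it during the trial, and read the estimate and its confidence interval against it.

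The cost is one paragraph and, optionally, one blinded calculation. No donors are added, and the test and conduct do not change. The drawback is that a single power figure gives way to a range.

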#### Statistical analysis

The primary endpoint is the number of days from surgery to return to normal physical activity. This will be assessed using the Katz ADL questionnaire. The primary analysis will test the following hypotheses:

H_0_ μ_Pfannenstiel_ ≥ μ_Periumbilical_

H_1_ μ_Pfannenstiel_ < μ_Periumbilical_,

where μ_Pfannenstiel_ and μ_Periumbilical_ are the mean number of days in the respective intervention groups. The primary endpoint will be compared between the intervention groups using a Student’s *t* test and a one-sided significance level of 5%. Additionally, a Mann-Whitney *U* test will be performed for sensitivity analysis. According to the intention-to-treat approach, all patients will be analyzed in the group to which they were randomized.

All secondary outcomes will be analyzed using appropriate summary measures depending on the distribution of the data and descriptive *p* values. Categorical data will be presented as absolute and relative frequencies. Continuous data will be presented as mean values with standard deviations and by median values with interquartile ranges, minimum values, and maximum values. Statistical analysis will be performed using SPSS version 24.0 (SPSS, Inc., Chicago, IL, USA). A statistical analysis plan will be developed by the principal investigator by the end of recruitment.

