**Fig. 1 Fig1:**
[figure not shown]
Study design flow chart. *Preoperative assessments including date of birth, gender, weight (kg), height (cm), and American Society of Anesthesiologists score. **Return to normal physical activity will be self-assessed using the Katz Basic Activities of Daily Living self-maintenance questionnaire during the first 4 postoperative weeks until all normal activities are recovered. *PEFR* peak expiratory flow rate, *PNF* primary non-function, *DGF* delayed graft function, *GFR* glomerular filtration rate, *IPAQ-SF* International Physical Activity Questionnaire-Short Form

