#### Secondary endpoints

Intraoperative outcomes, including estimated blood loss, warm ischemia time, and operating time, will be reported. In addition to the Katz ADL questionnaire, a physical activity score will be determined using the International Physical Activity Questionnaire-Short Form (IPAQ-SF). The IPAQ-SF score will be calculated before the operation and at POWs 2, 4, and 8. Postoperative pain will be assessed using the visual analog scale (VAS 0–10, 0 = no pain and 10 = unbearable distress) and by measuring in-hospital rescue analgesics until discharge. The peak expiratory flow rate (PEFR) will also be evaluated preoperatively and until discharge as an objective surrogate measure of pain. Length of hospital stay, time to return to work, postoperative complications, and all-cause mortality will also be reported in living donors. The appearance of incision scars will be evaluated with a patient satisfaction score (Likert scale 1–5, with 5 indicating strongly satisfied and 1 indicating strongly unsatisfied) and a cosmetic score (defined by the Stony Brook Scar Evaluation Scale [20]) during the first eight POWs. Possible incisional hernia at the site of the surgical incision will be examined by palpation and ultrasonography during each visit. The quality of the procured graft will also be evaluated in recipients after both procedures. Delayed graft function, primary non-function, serum creatinine levels, and glomerular filtration rates will be assessed in recipients until POW 4. Secondary outcome measures are defined in Table 1.

**Table 1 Tab1:** Secondary endpoints of the HAPERPACT trial

Secondary endpoints	Definitions
Warm ischemia time	From the time of clamping the first renal artery in situ to flushing the kidney with chilled solution on the back table (minutes)
Intraoperative complications	Any complication occurring during the operation
Estimated blood loss	The entire blood loss from skin incision to skin closure (milliliters)
Operating time	From the time of skin incision to closure of the skin incision (minutes)
Postoperative pain	Severity of pain measured by the 11-point visual analog scale (0 = no pain and 10 = unbearable distress)
Rescue analgesic	Total amount of analgesics required during the first three postoperative days
Peak expiratory flow rate (PEFR)	Maximum speed of expiration, measured with a peak flow meter

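### The primary t test is valid but unadjusted; adjusting for age and preoperative IPAQ-SF, both already recorded, may gain precision if they predict recovery time

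*Protocol article*

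**What the plan says.** The Statistical analysis section of the protocol article states the hypotheses as a difference in mean days and then names the test: "The primary endpoint will be compared between the intervention groups" by a Student's t test, one-sided at 5%. A Mann-Whitney U "test will be performed for sensitivity analysis". Neither test is described as adjusted for anything.

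The Randomization and blinding section describes block randomization and names no stratification factor.

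Two candidate covariates are already in the data plan:
- **Preoperative activity.** Under Secondary endpoints, "The IPAQ-SF score will be calculated before the operation and at POWs 2, 4, and 8". Table 1 also lists a preoperative IPAQ-SF assessment.
- **Age.** The Fig. 1 legend lists the preoperative assessments as "date of birth, gender, weight (kg), height (cm), and American Society of Anesthesiologists score". Age follows from date of birth.

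The Katz ADL, which defines the primary endpoint, is not given before surgery because every donor is taken to be independent in all six functions. The outcome therefore has no measured baseline of its own.

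The analysis plan is still to be written, by the end of recruitment.

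**The concern.** The endpoint is the number of days to regain six basic functions after major surgery. Age and prior physical activity are plausible predictors of how fast that happens. Eligibility sets only a lower age limit, so donors may differ widely. Adjustment does not need a baseline score on the same instrument, only a baseline variable that predicts the outcome, so the missing preoperative Katz score is no obstacle.

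As described, neither the randomization nor the analysis uses baseline prognosis. With 22 donors per arm, the standardized difference between arms in any one baseline variable has a standard deviation of √(2/22) = 0.30. It therefore exceeds 0.3 SD in either direction in about 32% of randomizations. If the variable is prognostic, that imbalance adds noise to the unadjusted difference, and a linear model would remove it.

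What is at stake is power and the width of the confidence interval in a small single-centre trial, not the validity of the test.

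**Working it through.** **Inputs from the Sample size section.** "A one-sided significance level of α = 0.05, a power of 80" per cent; "we used a difference of 10 days for sample size calculation"; "The standard deviation is expected to be 13 days"; 22 donors per group; 15% drop-out; 26 enrolled per arm.

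**Step 1: the plan's own figure.** For the unadjusted t test with n per arm, SE = 13 × √(2/n), noncentrality = 10/SE and df = 2n − 2.
- n = 22: SE = 13 × √(2/22) = 3.92; noncentrality = 2.55; df = 42; power 80.6%.
- n = 21: power 79.0%.

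So 22 per group is the smallest number that reaches 80%, as stated. Drop-out: 22/0.85 = 25.9, rounded up to 26 per arm, 52 in all. If all 52 are analysed, power is 86.2%.

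**Step 2: the adjusted model.** Let p covariates explain a share R² of the variance within arms. Three things change:
- The residual SD becomes 13 × √(1 − R²).
- The degrees of freedom fall by p, to 2n − 2 − p.
- Estimating p slopes when the covariates are imbalanced by chance inflates the variance by about 1 + p/(N − p − 3), with N = 2n. For p = 2 and N = 44 this is 1 + 2/39 = 1.051.

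Hence SE = 13 × √[(1 − R²) × (1 + p/(N − p − 3)) × 2/n].

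Example with R² = 0.20, p = 2, n = 22: 13 × √(0.80 × 1.051 × 0.0909) = 3.59 days; noncentrality 10/3.59 = 2.78; df = 40; power 86.2%.

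**Step 3: results.** R² is an assumption throughout.

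| Covariates R² | SE, 22 per arm (days) | Power, 22 per arm | Power, 26 per arm |
|---|---|---|---|
| Unadjusted | 3.92 | 80.6% | 86.2% |
| 0 | 4.02 | 78.8% | 84.9% |
| 0.05 | 3.92 | 80.6% | 86.5% |
| 0.10 | 3.81 | 82.5% | 88.1% |
| 0.20 | 3.59 | 86.2% | 91.1% |
| 0.30 | 3.36 | 89.9% | 94.0% |

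**Step 4: break-even.** The standard errors are equal when (1 − R²) × (1 + 2/39) = 1, that is R² = 1 − 39/41 = 0.049. Equating power instead of SE gives 0.050.

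With one covariate the inflation is 1 + 1/40 = 1.025. Break-even is then an R² of about 0.025, and power at R² = 0 is 79.8%, a loss of about 0.9 points.

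**The case against.** The strongest case against is that nothing here is wrong. Under randomization the unadjusted t test is valid, it matches hypotheses stated as means, and it is the test for which the trial was sized. No stratification factor is left out of the analysis, because none is named. Chance imbalance is already part of the sampling variance that the t test's standard error covers. All of this stands.

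It can also be said that the benefit is unproven. The endpoint is regaining basic self-care in donors who could all do it before surgery, whereas IPAQ-SF measures physical activity, a different construct. In screened donors the correlation could be near zero. This stands too: the article gives no R². It does not show that R² is small, though. A uniform preoperative Katz score rules out Katz as a covariate and says nothing about whether age or activity predicts recovery time.

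A reader might infer that precision is certainly being lost, or that adjustment is free. The documents support neither. Below an R² of about 0.05 the adjusted model is slightly worse, and at R² = 0 it drops just under the planned 80% with 44 donors. Nor is 44 necessarily the number analysed: 52 are to be enrolled, and intention-to-treat covers all who are randomized.

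Supportive adjusted analyses are commonly left to the analysis plan. The primary test is not left open here, however; the article names it.

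**Conclusion.** The point holds as a cheap, optional improvement, not as an error in the plan. The primary analysis is unadjusted and the randomization unstratified as described, while two plausible prognostic variables are recorded anyway.

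The trade-off is asymmetric. With two covariates and 44 donors, the worst case is a loss of about 1.8 points of power (80.6% to 78.8%). The gain is 5.6 points at an R² of 0.20 and 9.3 points at 0.30. With 52 donors the worst case is about 1.3 points (86.2% to 84.9%).

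These figures rest on the plan's own difference of 10 days and SD of 13 days, on roughly linear effects of the covariates, and on an assumed R². Whether precision is in fact gained depends entirely on that last quantity.

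**What to change.** In the analysis plan, before any outcome data are seen, specify the following:
- **Primary analysis:** a linear model of days to return to normal physical activity on arm, age and log-transformed preoperative IPAQ-SF, for example log(x + 1), with the arm term tested one-sided at 5%. The target stays the difference in mean days.
- **Sensitivity analyses:** the unadjusted Student's t test and the Mann-Whitney U test.
- **Missing baseline values:** simple imputation, for example the mean over both arms, so that no randomized donor is dropped for lack of a covariate.

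If the team doubts that both covariates are prognostic, a single one lowers break-even to an R² of about 0.02 to 0.03 and the worst-case loss to about 0.9 points.

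The cost is a few sentences, two degrees of freedom and the small possible loss of power given above. No new data are needed and the sample size need not change. Because the test is named in the published article, the change should be recorded openly as an amendment with its date. The timing matters because covariates chosen after outcomes are known carry little weight, above all for a self-reported endpoint that the Discussion concedes cannot be assessed blind.
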